### 1.2.3 Trial objectives

To compare weekly remote monitoring-driven management (RCP) with usual care (UCP) for patients with heart failure, who have cardiac implanted electronic devices (ICD, CRT-D or CRT-P).

### **1.2.4 Participants**

Patients with heart failure who are implanted with an ICD, CRT-D or CRT-P device with remote monitoring capabilities. Patients must be on stable medical therapy for at least 6 weeks prior to recruitment and have had a device implant for at least 6 months.

### 1.2.5 Intervention

The remote care pathway (RCP) was informed by clinical experience and a review of the literature consisting of procedures to deal with heart failure, arrhythmia and device management. There will be weekly telemetering of data (downloads) and protocol-driven changes in care co-ordinated by the study site remote monitor. This care will be delivered through telephone support, primary care contact or direct patient contact.

### 1.2.6 Study Hypothesis

We hypothesise that patient-independent remote monitoring using implanted device technology and deployed in clinical pathways designed for chronic management of heart failure in the home, will significantly reduce all-cause patient mortality and cardiovascular hospitalisation in the context of NHS care and will be more cost effective than usual care.

# Section 2. Design Issues

## 2.1 Study Design

This is a randomised, multi-centre, open label (non-blinded), parallel group, clinical trial in which patients are randomised to receive either the control (UCP) or intervention (RCP) pathways on a 1:1 basis.

## 2.2 Randomisation procedure

Subjects who met the inclusion criteria and did not meet any of the exclusion criteria were then given information about the trial. After giving informed consent each subject was then randomised to one of two management pathways; optimal medical management (UCP) or optimal medical management informed by weekly remote monitoring of the data from their implanted device (RCP) in a 1:1 ratio. Randomisation was performed centrally, by an external agency (Tenalea, The Netherlands) via a study-specific ECRF management system. The randomisation schedule was stratified by recruiting site and device type, with randomly permuted block sizes of either four or six patients per block.

## 2.3 Study Power and Sample Size

Our sample size calculation is driven by a required number of events and uses event rate estimates from previous studies: this is an event-driven trial. The UCP group event rate is estimated from the COMPANION^2^ and CARE-HF^3^ trials, that both had a patient population that we expect to be comparable to our study control group. These trials reported 48% for any death or CV disease hospitalisation at 2 years, and 39% at 29 months for CV death or unplanned hospitalisation, respectively. We anticipate slightly lower rates in this trial due to an improvement in routine care, and so assume a 40% event rate for our primary endpoint of all-cause mortality or unplanned CV hospitalisation (see 3.2.1) in the control arm at 2 years.

The meta-analysis of Clark et al^4^ that looked at telemonitoring or structured telephone support, reported a 20% risk reduction compared to usual care. Hence we assume that the intervention group will have an event rate of 32% at two years. This reduction in event rate (from 40% to 32%) at two years, if seen, would be clinically relevant.

Fixing a 5% (2-sided) significance level and 90% power, 546 events are needed to detect this effect size in a log-rank survival comparison of the two trial groups. To achieve this number of events we are likely to require 1394 patients in total (697 per group) with a minimum follow-up of 2 years. We will inflate this total by approximately 20% to allow for attrition, giving a final recruitment figure of 1650. This sample size would also be sufficient to provide a reasonable estimate of the effect size in the individual components of the primary outcome – ACM and CV disease related unplanned hospitalisation. This sample size is considered feasible within the trial timescales.

## 2.4 Data Collection, storage and management

### 2.4.1 Data Collection

An electronic clinical report form (eCRF) was utilised to capture healthcare utilisation elements, QoL assessment and clinical events on a patient-by-patient basis. This should allow for an accurate and comprehensive assessment of the care pathway. All aspects of local data recording and management are the responsibility of the remote monitor lead in each site.

All participants will complete the SF-12, EQ5D-3L and KCCQ at enrolment, 3 months, 6 months, 12 months and 24 months. These tools were administered by the study remote monitor leads in each centre. The initial health-related quality of life forms were completed at the time of patient enrolment in the hospital. Subsequent assessments were performed by the patients in their homes. The forms were sent to them by post with the necessary means for return of the forms. Receipt of the forms and their return were managed by the remote monitors and local study administration staff.

### 2.4.2 Data Storage

The original data are kept in each of the participating centres and conform to all necessary Data Protection Requirements. The data are also kept electronically on the TENALEA server, under the same European data protection regulations.

### 2.4.3 Classification / confirmation of events

All events suspected to be a primary or secondary outcome event will be adjudicated by two clinical experts on the Endpoint Review Committee (ERC). During this review each event will be classified according to the procedural rules of the ERC (see Appendix 1: 7.1).

### 2.4.4 Data Management

Prior to any statistical analysis, data will be exported by TENALEA as a series of SAS datasets. These SAS datasets will then be merged to produce the trial database. The trial database will be checked for missing, impossible and improbable values. Impossible and improbable values will be defined by clinical opinion/expertise. Improbable values will also include values that are outside three standard deviations of the mean value. Any questions regarding the data will go back to the trial data manager for possible referral back to the recruiting site. The final database will be locked for analysis once the ERC has classified all events and all identified data queries have been closed.

## 2.5 Data monitoring and interim analyses

### 2.5.1 Planned Interim analyses

An Independent DSMB reviewed recruitment, data completeness, primary outcome data, and safety of remote monitoring during the study. To facilitate the DSMB there was one planned interim analysis at 400 primary endpoint events (ACM or CV related hospitalisation) focusing on safety and the primary outcome. An independent statistician produced the analysis and presented the results to the DSMB. The independent statistician and the DSMB were not blinded to the treatment allocation.

### 2.5.2 Rules for stopping the trial and adjustment of the significance level

The DSMB had the ability to stop the trial early on safety grounds (see terms of reference for the DSMB – Appendix 2: 7.2) but in addition to this a formal stopping rule was instigated for the analysis of the primary outcome at 400 events. The threshold for significance at the time of the interim analysis was set at requiring a p value of <0.001. Setting the interim significance threshold at this level retained a threshold of p=0.048 for the final analysis using the Peto-Haybittle rule, whilst maintaining an overall 5% false positive error rate.

# Section 3. Statistical Analyses

## 3.1 Definition of Analysis Populations

### 3.1.1 Intention-to-treat population (ITT)

The primary analysis population is the Intention-To-Treat (ITT) population. The ITT population consists of all randomised subjects, with each subject analysed as part of the group to which they were randomised. All randomised participants will be included, including any subjects who are later found to be ineligible and those who do not follow the trial protocol.

### 3.1.2 Per-Protocol population (PP)

The PP population consists of all randomised patients who did not experience any major protocol violation within the first two years of follow up.

Protocol violations are any unapproved changes in the research study design and/or procedures that are within the investigator’s control and not in accordance with the IEC/IRB-approved protocol that may affect the participant’s rights, safety or well-being, or the completeness, accuracy and reliability of the study data. Classification of protocol violations will be done by an authorised core group of the TSC after review of a blinded list of protocol violations that occurred in the trial, but before the date of code break.

Protocol violations include enrolment of ineligible trial participants and application of study treatment other than by randomisation or other than as described in the study protocol.

Participants in the intervention arm (RCP) for whom we have less than 75% of their weekly remote monitoring downloads available (within the first two years) will be considered as major protocol violators. With regard to assessing compliance with data downloads, the weeks where a participant has been admitted to hospital (or is still a hospital inpatient) will be ignored - although remote monitoring may not occur during this period the patient will be being monitored locally.

The use of the 75% remote monitoring threshold as a definition of compliance with the protocol will be explored as one of the extended analyses.

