### 3.7.2 Proportion of remote monitoring for inclusion in per protocol Analysis

The threshold used for including participants in the PP analysis set, based on their percentage of remote monitoring that was conducted, will be explored. A range of different threshold percentages for successful monitoring will be used, with the impact on the treatment effect examined. This will enable us to explore whether the completeness of the monitoring has any impact on its effectiveness.

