## 3.9 Sensitivity Analyses

The primary and secondary endpoints as well as the final models from the extended analyses will also be evaluated in the PP population, to investigate the sensitivity of the results. This sensitivity analysis will only be performed if the number of major protocol violations suggests that the main results may change.

The primary and secondary analyses will also be replicated using multiple imputation to assess the impact of the missing data values (where applicable).

In addition, sensitivity analyses will be performed on the secondary endpoints for the CV death ‘equivalent’ events - heart transplantation, appropriate shock from ICD, LTAD insertion and survived resuscitation of sudden cardiac arrest.

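### The one-arm 75% download rule for the per-protocol set does not say how weeks after death or exit count, and it selects RCP patients on post-randomisation adherence

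*Combined protocol and SAP*

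**What the plan says.** SAP 3.1.2 defines the PP population as "all randomised patients who did not experience any major protocol violation within the first two years of follow up". For the intervention arm it adds a numerical criterion: RCP participants with "less than 75% of their weekly remote monitoring downloads available (within the first two years) will be considered as major protocol violators". One kind of week is taken out of the count: "the weeks where a participant has been admitted to hospital (or is still a hospital inpatient) will be ignored". The section does not mention weeks after death, withdrawal or loss to follow-up, nor weeks after elective heart transplantation, which the ERC charter (SAP 7.1) treats as a study exit. UCP patients have no adherence criterion.

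The PP set is used in two places. In SAP 3.9 the primary and secondary endpoints "will also be evaluated in the PP population, to investigate the sensitivity of the results", on condition that the number of major violations suggests the main results may change. SAP 3.7.2 carries no such condition: "A range of different threshold percentages for successful monitoring will be used, with the impact on the treatment effect examined". Its stated purpose is to learn whether completeness of monitoring affects how well monitoring works. SAP 6.1.2 plans Tables 64 to 68 as PP copies of the main outcome tables, including mortality and health economics.

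**The concern.** Death is a component of the primary endpoint. If weeks after death are scored as missed downloads, an RCP patient who transmitted every week and then died in the first 18 months becomes a major violator and leaves the analysis. A UCP patient with the same course stays. The rule would then select on the outcome in one arm only and favour remote monitoring. The same holds for RCP patients who withdraw or are lost early, although their effect on the event rate is less direct.

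Raising the threshold in 3.7.2 would remove more RCP deaths, so the estimated effect would grow with the threshold even if monitoring did nothing. That could be read as evidence that fuller monitoring works better. Early deaths would also be counted among the major violations, which makes it more likely that the condition in 3.9 is met.

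A different definition of the denominator does not remove every problem. Adherence is observed after randomisation and restricted in one arm, so the PP comparison is between selected RCP patients and all UCP patients. SAP 3.7.3 gives a caution about this for the on-monitoring analysis; 3.1.2, 3.7.2 and 3.9 do not.

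**Working it through.** **Inputs from SAP 2.3.** For UCP at two years the authors "assume a 40% event rate for our primary endpoint of all-cause mortality or unplanned CV hospitalisation". For RCP: "Hence we assume that the intervention group will have an event rate of 32% at two years". On size: "Fixing a 5% (2-sided) significance level and 90% power, 546 events are needed to detect this effect size". The target is 825 per arm (SAP 1.2.2).

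**The plan's own figure.** Under proportional hazards the design HR is ln(0.68)/ln(0.60) = 0.755. The Freedman formula gives 540 events and Schoenfeld gives 533, which are 1.1% and 2.4% below 546. The plan's figure is reproduced, and 0.755 is the yardstick below.

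**Assumptions.** The documents give no mortality rate, so two-year mortality m is taken as 5% to 20% with constant hazard. There is no true effect (40% composite events in both arms), and downloading is perfect while alive. The cut-off falls at 0.75 × 104 = week 78.

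**Closed form at two years, if weeks after death count as missing.** The proportion dead by week 78 is d = 1 − (1 − m)^0.75. All of these patients are composite events, so the RCP rate in the PP set is (0.40 − d)/(1 − d). The HR is ln(1 − rate)/ln(0.60).

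| m | d | RCP patients dropped (825 × d) | RCP rate | Risk ratio | HR |
|---|---|---|---|---|---|
| 5% | 0.038 | 31 | 37.7% | 0.94 | 0.925 |
| 10% | 0.076 | 63 | 35.1% | 0.88 | 0.845 |
| 15% | 0.115 | 95 | 32.2% | 0.81 | 0.761 |
| 20% | 0.154 | 127 | 29.1% | 0.73 | 0.672 |

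The false effect equals the design effect when (0.40 − d)/(1 − d) = 0.32. This gives d = 0.08/0.68 = 0.118, and m = 1 − (1 − 0.118)^(4/3) = 15.4%.

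**Cox model over the planned follow-up.** The protocol timetable (section 13) implies follow-up of 2 to about 3.8 years, if recruitment runs over months 2 to 24 and follow-up to month 48. An illness-death model was simulated with 825 per arm, 300 trials per scenario, and a death hazard three times higher after a first CV hospitalisation. A false benefit means z below −1.96, expected in 2.5% of trials if there were no bias.

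| m | RCP patients dropped | Composite HR | Trials with false benefit | HR for death |
|---|---|---|---|---|
| 5% | 29 | 0.94 | 12% | 0.56 |
| 10% | 60 | 0.88 | 42% | 0.55 |
| 15% | 90 | 0.82 | 82% | 0.53 |
| 20% | 122 | 0.75 | 98% | 0.51 |

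Changing the hazard multiplier to 1, 2 or 5 moves the 15% result only between 0.81 and 0.82.

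**Threshold exploration (m = 15%, same model).** Thresholds of 50%, 60%, 75% and 90% give null HRs of 0.88, 0.85, 0.82 and 0.78.

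**If only the patient's own weeks under follow-up count (m = 15%).** With perfect downloading nobody is dropped, and the HR is 1.00 for the composite and for death. With mean adherence of 90%, about 25 RCP patients are dropped and the HR is still 1.00. The rule that counts weeks after death drops about 123 and gives 0.80.

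**What remains under that reading.** The 1.00 arises because adherence was simulated independently of risk. Suppose a share q of RCP patients is dropped and their true two-year event rate is r. The PP rate is then (0.40 − q·r)/(1 − q). These values of q and r are illustrations, not figures from the documents:
- q = 10%, r = 30%: (0.40 − 0.03)/0.90 = 41.1%, risk ratio 1.03.
- q = 10%, r = 60%: (0.40 − 0.06)/0.90 = 37.8%, risk ratio 0.94.
- q = 20%, r = 60%: (0.40 − 0.12)/0.80 = 35.0%, risk ratio 0.88.

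The sign depends on whether poor adherers are at higher or lower risk, which the plan cannot know in advance.

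**The case against.** The strongest reply is that the SAP never fixes a 104-week denominator. It speaks of each patient's own downloads and of two years of follow-up, and follow-up ends at death. It also describes violations as matters within the investigator's control, which death is not. On that reading no patient is excluded for dying. This stands: a reader might infer that the rule certainly scores weeks after death as missed, but the text leaves it open. The ambiguity still matters, because two analysts following the same SAP could report null hazard ratios of 1.00 and about 0.8.

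The PP analysis is also a conditional sensitivity analysis, and the primary and secondary analyses are ITT. That stands and limits the seriousness. The condition in 3.9 does not, however, cover the exploration in 3.7.2.

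A third reply is that 3.7.2 is labelled exploratory, and that the authors show in 3.7.3 that they understand the loss of randomisation. That is fair, but the caution is attached only to the on-monitoring model.

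Two further criticisms would go too far. Weeks after discharge from a first CV admission are properly counted, since monitoring is still due. The rule also does not remove deaths alone: living non-adherent RCP patients go too and, if weeks after exit count, so do early withdrawals and losses.

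**Conclusion.** The concern holds as a defect in a supporting analysis. The denominator in 3.1.2 is undefined for weeks after death or exit. If those weeks count as missing, the PP hazard ratio with no true effect is about 0.94 to 0.75 over assumed two-year mortality of 5% to 20%, and 3.7.2 produces a gradient by itself. If they do not count, the death artefact is nil, but selection on adherence in one arm remains, with unknown sign.

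A reader might infer that the false benefit is as large as the design effect. That requires two-year mortality of about 15% if follow-up stops at two years, or about 20% with follow-up to 3.8 years. The documents support neither figure. A reader might also infer that the primary result is at risk. It is not: the ITT analysis does not use this rule. The change is worth making before code break, but the main conclusion does not depend on it.

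**What to change.** - **SAP 3.1.2:** define the denominator as weeks within the first two years in which the participant is alive, under follow-up and not an inpatient. State that weeks after death, withdrawal, loss to follow-up or study exit are not counted, and that weeks after discharge from a first CV admission are.
- **SAP 3.7.2 and 3.9:** make a randomisation-based complier estimate the main adherence analysis, for example an instrumental-variable or structural failure-time model using randomised arm. Keep the PP and threshold results as descriptive, with the caution that 3.7.3 already gives on loss of randomisation.

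The cost is a few sentences of SAP text and one extra model on data already held. The complier estimate will have a wider interval than the naive PP estimate.

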## 3.2 Trial Endpoints

### 3.2.1 Primary Endpoint

The primary endpoint is the time to first event of either All-Cause Mortality (ACM) or unplanned Cardiovascular (CV) hospitalisation.

Cardiovascular mortality and unplanned cardiovascular hospitalisation will be evaluated by the Endpoint Review Committee (ERC), as outlined in Appendix 1: 7.1. Definitions will be documented in full in the procedural rules of the ERC. Death will be classified as cardiovascular unless an unequivocal non-cardiovascular cause of death has occurred. The extended analyses will include sensitivity analyses around the classifications.

### 3.2.2 Secondary Endpoints

The secondary endpoints of the trial are:

1. Time to death.
2. Time to a cardiovascular related death.
3. Time to a non-cardiovascular related death.
4. Time to first unplanned hospitalisation for cardiovascular reasons or cardiovascular related death.
5. Time to first unplanned hospitalisation for non-cardiovascular reasons or death by any cause.
6. Time to first unplanned hospitalisation for cardiovascular reasons.
7. Time to first unplanned hospitalisation for non-cardiovascular reasons.
8. Total number of unplanned hospitalisations.
9. Total number of unplanned hospitalisations for cardiovascular reasons.
10. Change from baseline in SF12 scores at 2 years (physical and mental health components).
11. Change from baseline in EQ5D scores at 2 years.
12. Change from baseline in KCCQ at 2 years.
13. Change from baseline in SF12 scores at 1 year (physical and mental health components).
14. Change from baseline in EQ5D scores at 1 year.
15. Change from baseline in KCCQ at 1 year.
16. Number and cost of hospitalisations.
17. Difference in cost of resources consumed.
18. Difference in cost of cardiovascular related health care use.
19. Incremental costs per quality-adjusted life years (QALYs).

Unless otherwise stated, secondary endpoints will be measured at the last follow-up or at the last available observation within the two year follow-up period.

## 3.3 Subject disposition

The screening process will be described and details of why subjects failed screening will be summarised with frequency counts. The number of subjects enrolled into the study and the number of subjects enrolled but not randomised, together with the reasons for not being randomised, will also be summarised.

The number of randomised subjects and the number of subjects withdrawing consent will be summarised by treatment group.

The frequency of subjects enrolled in each recruiting site will be tabulated by randomised treatment group and for all randomised subjects combined. This will also be presented by device type.

## 3.4 Demographic and Baseline Characteristics

All demographic and baseline characteristics will be summarised by randomised treatment group. The distribution of continuous variables will be examined by assessing treatment group specific histograms. Variables that appear to be normally distributed will be summarised using means, standard deviations, minimum and maximum values. Variables that do not appear to be normally distributed will additionally be summarised with medians, lower and upper quartiles. Categorical variables will be summarised using frequency counts and percentages within each of the randomised treatment groups.

## 3.5 Primary Analysis

The primary analysis will be performed on the adjudicated events in the ITT population.

The main analysis will use a Cox proportional hazards model to derive the hazard ratio for the comparison between UCP and RCP. The stratifying variables of recruiting site and device type will be included in the model as fixed effect categorical variables. All estimates will be reported as hazard ratios (HR) and will be presented with 95% confidence intervals.

Subjects will be censored at the time of study end for those alive and free of unplanned cardiovascular hospitalisation, and at the last date known to be alive and free of such hospitalisation for those who are lost to follow-up (e.g., those who leave a study site area).

Time to event will be visualised using Kaplan-Meier curves.

